#### *11.1.5.2 Processing of Clinical Text and Feature Extraction*

Linguistic processing of clinical notes will be performed using the clinical Text Analysis and Knowledge Extraction System (cTAKES) (<http://ctakes.apache.org>). Pre-processing will generate lexical features tokens, part-of-speech (POS) tags, and chunks. The spans of Unified Medical Language System (UMLS)–named entity mentions (e.g., diseases, symptoms, anatomy, procedures) will be identified. Each named entity mention will be mapped to a UMLS concept unique identifier (CUI). For instance, the named entity mention for “opioid withdrawal” is assigned C0029104 as its CUI. The named entity mention of “opioid withdrawal” in the text of the note is mapped to a separate CUI than “history of opioid withdrawal,” which is C3266352. Each named entity mention will be subsequently analyzed to determine its negation status (e.g., “no opioid withdrawal”) using NegEx. This method of data processing mitigates lexical variations between providers. Additional UMLS semantic types will be included to accommodate items relevant to the task at hand, utilizing the latest dictionary lookup module from Apache cTAKES.

An additional set of features will be generated through examining n-grams. A term-frequency, inverse document-frequency (tf-idf) transformation will be used to weigh CUIs, features extracted from annotation, and other unigram and bigram features into normalized values for machine learning classifiers.

#### *11.1.5.3 Analysis with Supervised Machine Learning*

Discovering multiple phenotypes within an encounter can be framed as a multilabel classification problem. Multilabel classification assigns to each sample a set of target labels. In our context, this can be thought as predicting several phenotype properties of an encounter that are not mutually exclusive. We will assess a variety of machine learning methods within the multilabel classification task (e.g., ridge regression classifier, support vector machines, random forest, deep neural networks).

We will explore the use of several different features sets within the machine learning classifiers. A grid search with 10-fold cross-validation will be performed on the training dataset with examination of the classifiers and tuning performed within promising hyperparameter ranges. Then the AUC ROC curve scores will be compared to find the best classifiers, and the hyperparameters further tuned. A tournament-style process will be used to reduce the number of classifiers and hyperparameters through several iterations, until only a single best classifier and set of hyperparameters remain.

Discrimination of the ML-models will be evaluated with AUC ROC curves and 95% confidence interval (CI). Model calibration will be measured visually with calibration plots and formally tested with the Hosmer-Lemeshow goodness-of-fit test. Test characteristics including total accuracy, sensitivity, specificity, negative predictive value (NPV), and positive predictive value (PPV) will be

examined to compare between NLP classifiers and the rule-based approach on the internal validation data set. Adding the ML-based approach to the rule-based approach will be examined for improved performance using the net reclassification improvement (NRI) and integrated discrimination improvement (IDI) measures. As mentioned above, a learning curve will be generated to investigate the effect of sample size on classifier performance as an approach to assess adequacy of statistical power.

Throughout the development and validation of the phenotypes, we will adhere to general coding practices to ensure quality including aspects that ensure readable, reusable, and testable components that are all side effects of writing modular code. Due to the limited size of the project we will forego more sophisticated techniques used when collaborating including pair programming and issue tracking.

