#### 11.1.2.3 Sampling strategy

Because the prevalence of potential phenotypes within the general population is low, simple random sampling from the entire population would require a prohibitively large sample size. Moreover, machine learning methods often are enhanced through better balanced datasets. We will therefore randomly oversample from each phenotype strata to ensure adequate numbers of patients with positive phenotypes as determined by sample size calculations. Initial phenotype sampling will be achieved by application of inclusion/exclusion rules developed through the case definitions.

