#### 11.1.2.4 Sample Size determination

Following conventional machine learning methodology, we will randomly partition the data into 80% training and 20% validation sets. We will base our sample size determination on the validation cohort size.

Previous literature has indicated that ICD codes have general high specificity (few false positives) for disease entities within EHR systems, but low sensitivity (large number of false negatives). Development of phenotypes often significantly improve the sensitivity while maintaining specificity. Conservatively, we estimate that we will be able to achieve a specificity of 95% and sensitivity of 70%. We assume 50% prevalence due to oversampling for each phenotype, 80% power, and significance level of 0.05. Based on these assumptions we estimate needing 75 cases per phenotype in the validation cohort to achieve a one-sided lower confidence level limit of 15%. For the total cohort, based on the 80/20 split, we will need ~ 375 cases per phenotype. We additionally will optimize estimation of sensitivity and specificity in the setting of verification bias using the methods developed by Begg and Greens.

We will continually monitor the performance of the development model as its dependence on the sample size through learning curves. If through visual inspection, the performance of the development model plateaus prior to reaching the full sample size, we will stop further data collection on the development data set.

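### Predictive values, accuracy and calibration of the EHR phenotypes are to be estimated, unweighted, on a validation set enriched to about 50% prevalence, so for the refined rules and ML/NLP classifiers they do not carry over to ED use

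*Combined protocol and SAP*

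**What the plan says.** Protocol section 11.1.2.3 explains the sampling. "Because the prevalence of potential phenotypes within the general population is low", simple random sampling is judged too large, and so "We will therefore randomly oversample from each phenotype strata to ensure adequate numbers of patients with positive phenotypes". The strata come from the initial rule-based case definitions, written as SQL queries under section 11.1.1, and not from true status.

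Section 11.1.2.4 sets the size. "We assume 50% prevalence due to oversampling for each phenotype, 80% power, and significance level of 0.05". "Conservatively, we estimate that we will be able to achieve a specificity of 95% and sensitivity of 70" per cent. On that basis "we estimate needing 75 cases per phenotype in the validation cohort to achieve a one-sided lower confidence level limit of 15" per cent. The validation set is not drawn separately: "we will randomly partition the data into 80% training and 20% validation sets". The same section adds a Begg and Greenes step for verification bias, worded for sensitivity and specificity.

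Section 11.1.5.3 lists the measures: "Test characteristics including total accuracy, sensitivity, specificity, negative predictive value (NPV), and positive predictive value (PPV) will be" examined on the internal validation set, to compare the NLP classifiers with the rule-based approach. It also assesses calibration of the ML models by plots and the Hosmer-Lemeshow test. Section 11.1.4 says that the rule-based phenotypes follow a similar analysis plan. No section reweights PPV, NPV, accuracy or calibration to natural ED prevalence, or says that they will be labelled as sample-specific.

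**The concern.** Sensitivity and specificity condition on true status. PPV, NPV, total accuracy and calibration also depend on how common the phenotype is among the visits analysed. Here that share is set by design, and a random 20% split keeps it.

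Aim 4 (section 4.2.4) is listed among the primary aims, and its hypothesis is about accurate, automatic characterisation of presentations. The uses named in section 2.2.1 and section 11.0 are surveillance and finding potentially eligible patients. For both, the useful quantity is the fraction of flagged visits that are true cases at real ED frequency. A value from a half-and-half sample does not give that fraction. A model fitted and checked at 50% prevalence also has its calibration judged against the wrong base rate.

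**Working it through.** **Inputs.** From section 11.1.2.4: sensitivity Se = 0.70, specificity Sp = 0.95, sample prevalence 0.50, power 0.80, significance level 0.05, and 75 validation cases. ED prevalence p is not given beyond being low. The values 10%, 5% and 1% below are my assumptions.

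**The plan's own figure.** I read the 15% as a lower limit 15 points below the sensitivity, that is 0.70 against 0.55.

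- Exact binomial, one-sided 0.05: power stays at or above 0.80 from n = 73 and is 0.843 at n = 75.
- Normal approximation, two-sided: (1.960 + 0.842)² × 0.70 × 0.30 / 0.15² = 73.3, so 74.
- Total: 75 / 0.20 = 375, as stated ("For the total cohort, based on the 80/20 split, we will need ~ 375 cases per phenotype").

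The stated size is reproduced to within two cases and is not in question.

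**Prevalence-dependent measures.**

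- PPV = Se·p / [Se·p + (1 − Sp)(1 − p)]
- NPV = Sp(1 − p) / [Sp(1 − p) + (1 − Se)p]
- Accuracy = Se·p + Sp(1 − p)

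At p = 0.50:

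- PPV = 0.350 / (0.350 + 0.025) = 93.3%
- NPV = 0.475 / (0.475 + 0.150) = 76.0%
- Accuracy = 0.350 + 0.475 = 82.5%

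At p = 0.05:

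- PPV = 0.0350 / (0.0350 + 0.0475) = 42.4%
- NPV = 0.9025 / (0.9025 + 0.0150) = 98.4%
- Accuracy = 0.0350 + 0.9025 = 93.75%

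| Prevalence | PPV | NPV | Accuracy |
|---|---|---|---|
| 50% (plan's sample) | 93.3% | 76.0% | 82.5% |
| 10% (assumed) | 60.9% | 96.6% | 92.5% |
| 5% (assumed) | 42.4% | 98.4% | 93.75% |
| 1% (assumed) | 12.4% | 99.7% | 94.75% |

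Outside that range, PPV is 77.8% at 20% and 6.6% at 0.5%. For any prevalence below 50%, PPV from the enriched set is too high. With Sp above Se, NPV and accuracy are too low.

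**Can a comparison reverse?** Section 11.1.5.1 expects rule-based systems to be precise but to miss cases. Take, purely as an illustration, rules with Se 60% and Sp 98%, and an NLP classifier with Se 80% and Sp 90%.

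- At 50% prevalence: rules 0.300 + 0.490 = 79.0%; NLP 0.400 + 0.450 = 85.0%. NLP leads.
- At 5% prevalence: rules 0.030 + 0.931 = 96.1%; NLP 0.040 + 0.855 = 89.5%. Rules lead.

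**Limit of this model.** It holds Se and Sp fixed and changes only the share of true cases, as if sampling were on true status. Sampling is in fact on initial-rule strata. Random sampling within those strata preserves the initial rule's own PPV and NPV, and distorts its sensitivity and specificity. For the refined rules and the ML/NLP classifiers the predictive values do shift, but the table shows direction and possible size and does not forecast the result.

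**The case against.** **The measures serve only to compare two approaches on one data set.** The sentence in section 11.1.5.3 is indeed framed that way. At a common prevalence the PPV ranking depends only on Se/(1 − Sp) and the NPV ranking only on (1 − Se)/Sp, so those rankings survive. The accuracy ranking does not, as shown above. A reader might infer that the team will present about 93% as PPV in ED use. No section says so. The supportable statement is that nothing in the plan prevents it.

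**External validation will supply the real-world values.** Section 11.5 assigns generalisability to four sites, uses prospective screening by research assistants as the gold standard, and allows the algorithms to be modified. This is a partial answer. Sections 2.2.1 and 11.0 send only the rules-based phenotypes there, so for the ML/NLP classifiers the enriched internal set is the only evaluation described. The external chart review is also stratified on phenotype presence and absence. In section 8.4.1 trial screening draws on track boards and provider referral, so it is not clearly a natural-prevalence sample. Section 11.5 names neither PPV nor weighting.

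**The ML arm is only a benchmark.** Section 11.1.5.1 does describe it as a possible upper bound and a way to find data elements. That lowers the stakes for its calibration. It does not help the refined rules, which are the product to be deployed.

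**Everything in that section is distorted.** A reader might extend the point to the net reclassification and integrated discrimination measures. Both condition on true status, so prevalence reaches them only indirectly, through fitted risks or thresholds. They are not part of this point.

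**Conclusion.** The point holds for PPV, NPV, total accuracy and calibration of the refined rules and the ML/NLP classifiers. As written, the plan yields values tied to a sample whose case share was set by design. Begg and Greenes, as planned, corrects only sensitivity and specificity.

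Under the plan's own Se and Sp, PPV is 93.3% in the enriched sample. It would be between 60.9% and 12.4% if ED prevalence lay between 10% and 1%. A reader might take that range as the true PPV in ED use. The documents do not support this, because they give no prevalence figure and sampling is on rule strata. Nor are all the measures flattered: NPV and accuracy move the other way. I have no size for the calibration error.

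None of this touches the RCT's eligibility criteria or primary outcome. It bears on what can be claimed for Aim 4, and the plan should be changed before the phenotype results are reported.

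**What to change.** In sections 11.1.5.3 and 11.1.4, state one of the following.

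1. PPV, NPV, total accuracy and calibration are estimated with weights equal to the inverse of each encounter's sampling probability. Section 11.1 allows one encounter to carry several phenotypes, so strata overlap and the weight must use the encounter's overall inclusion probability. With two strata sampled independently at fractions a and b, that is 1 − (1 − a)(1 − b) for an encounter in both.
2. PPV and NPV are computed from the corrected sensitivity and specificity over a stated range of ED prevalence, for example 1%, 5% and 10%. This does not cover calibration, which still needs weights.

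Under either option, label any unweighted value as specific to the enriched sample, and base the accuracy comparison between rules and NLP on the weighted figures.

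The cost is modest: inclusion probabilities must be derived and recorded when the cohort is drawn, intervals become somewhat wider, and the reported PPV will look less favourable. The sample size need not change on this account.

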## 11.2 Figure 3: EHR Phenotype Process

[figure not shown]

### 11.3 Figure 4: Delphi Consensus Process

[figure not shown]

## **11.4 Translation Steps for Interoperability, Portability, and Scalability**

### **11.4.1 Translation to Common Data Model**

Identified metadata elements (e.g., type of lab, demographic) will be mapped to standard ontologies/vocabularies (ICD9-10, SNOMED, etc.) within the NIH/NLM Value Set Authority Center (VSAC), cross-checked and enhanced with UMLS concept identification through natural language processing (NLP) described below and eleMap software provided by PheKB (<https://phekb.org>), and organized within a common data model (CDM) such as PCORnet or OMOP CDM. Because we anticipate that some ED phenotype data elements will not be available in standard data models, we will augment the data model where necessary.

### **11.4.2 Scientific Container Development**

In order to support implementation of the OUD phenotypes and metrics within a distributed research network capable of surveillance, we will wrap the developed algorithms within scientific containers. Scientific containers enable secure, facile software deployment among disparate computing environments by including software dependencies and configuration with a virtualized environment. This provides for a more seamless distribution of the analytic engine and allows for the local processing of datasets, removing the need for external transfer of electronic protected health information (ePHI). This approach also allows scalability within a distributed research network and addresses calls by journal editors, funding agencies, governmental institutions, and individual scientists for the scientific community to embrace practices to support computational reproducibility.

## **11.5 Phenotype External Validation**

We will partner with four participating sites within the overarching trial to validate the EHR phenotypes. Data collected during screening, enrollment and EHR extraction will serve to verify the validity and generalizability of the electronically extracted EHR elements, the mapping process, and the phenotype definitions. Manual chart review will follow a process similar to the development stage and will be conducted at each site with stratification ensuring adequate coverage of all EHR phenotypes and their presence and absence. The primary purpose of the manual chart review will be to verify the validity and generalizability of the electronically extracted EHR elements, the mapping process, and the phenotype definitions. Recognizing that opioid-related phenotypes are not always faithfully captured in the EHR (e.g., failure to screen for opioid-related illness, failure to document prior drug use history or medications), prospective screening for opioid-related phenotypes will be conducted in the ED by RAs involved in enrollment for the trial and serve as the gold standard for phenotype comparison. Test characteristics for each ED opioid-related phenotype will be calculated. Data elements, phenotypic algorithms, and metrics will be modified if necessary, based on information obtained in the validation process.

For external validation at the four participating sites we will use the Western Institutional Review Board (WIRB). At each site for the medical chart review we will apply for waiver of informed consent in a similar process to the development and internal validation stages. For prospective

screening in the ED we will align procedures with the compound authorization form for the clinical trial component.

11.6 Figure 5: ED Phenotype Timeline

[figure not shown]

## 12.0 STATISTICAL DESIGN

This study aims to test two hypotheses:

1. Implementation outcome: Approximately 80% (24) of sites will achieve competence in both BUP induction procedures.
2. Effectiveness outcome: There will be a higher proportion of patients engaged in formal addiction treatment on the 7th day post randomization in those randomized to XR-BUP compared to those randomized to SL-BUP.

### 12.1 Definition of Primary Implementation Outcome

The primary implementation outcome will be competence in ED-initiated XR-BUP and SL-BUP inductions. This will be a binary site-level variable indicating that the site has met all criteria on the site initiation checklist.

### 12.2 Definition of Primary Effectiveness Outcome

The primary effectiveness outcome will be engagement in formal addiction treatment at 7 days. This will be a binary variable, classified as engaged or not engaged. Self-reported engagement will be verified with the treatment provider.

#### 12.2.1 Experimental Design

This is a Hybrid Type 1 Effectiveness-Implementation design. The study will use well developed IF procedures and resources to train approximately 30 sites to competence in ED-initiated BUP using standard and XR-BUP inductions. Sites will be evaluated for the implementation aims using the 6-item checklist and EDs will be compared before and after implementation (detailed in CTN 0069 and CTN 0079) for outcomes including # of physicians with waivers, BUP doses administered and prescribed, etc. In an embedded randomized trial utilizing sites on a rolling basis as they are trained to competence, we will compare the effectiveness of Standard SL-BUP induction with that of XR-BUP. Eligible ED patients with moderate to severe OUD will be consented and enrolled. Patients with COWS  $\geq 8$  will receive an initial 4 mg dose of BUP. If after 30 minutes they experience no worsening in withdrawal symptoms, they will be randomized in a 1:1 to either SL or XR BUP. The primary outcome will be engagement in formal addiction treatment at 7 days.

#### 12.2.2 Primary Statistical Hypothesis

Based on our primary aim and primary outcome, we hypothesize that the probability of treatment engagement at 7 days is greater among participants with OUD in the XR-BUP *arm* versus those in the SL-BUP *arm*, *i.e.*, treatment is superior in XR compared to SL.

We use probability  $p_{XR}$  to represent the probability of treatment engagement for a subject in the XR *arm*, and the probability  $p_{SL}$  for the probability of treatment engagement for a subject in the SL *arm*. Treatment superiority is operationally defined in terms of the odds ratio,  $OR = [p_{XR} * (1 - p_{SL})] / [p_{SL} * (1 - p_{XR})]$ . Thus, the primary statistical hypotheses are:

$H_0: OR = 1$ , i.e., XR is not superior to SL

$H_A: OR \neq 1$ , i.e., XR is different than SL

ORs >1 will indicate superiority of XR over SL with regard to the treatment engagement outcome.

### 12.3 Sample Size Justification for Evaluation of Effectiveness

For the comparison of XR vs. Standard SL-BUP, the primary effectiveness outcome will be engagement in formal addiction treatment at 7 days, classified as engaged or not engaged based on verification with the treatment provider. A sample size of 850 per group is required to ensure 90% power at the 2-sided 0.05 significance level to detect a difference in the proportion engaged of 8% between SL and XR-BUP (i.e., 45% engaged in SL vs. 53% engaged in XR-BUP). We will enroll approximately 2000 patients to accommodate a 15% dropout. Figure 6 below shows the sensitivity of the power of the study given variations in the proportions of those engaged in treatment. Regardless of the proportion engaged in treatment in the SL group, our sample size will provide > 90% to detect improvements for the XR group of 8% and > 80% to detect improvements of 7%. This sample size will also provide sufficient power to detect differences in notable subgroups (treatment seeking, rural/urban, insurance Y/N).

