#### 8.4.4 Randomization Procedures

Eligible participants will be randomized in a 1:1 ratio to XR-BUP or SL-BUP. The randomization process will be performed by computer by the DSC. A permuted block randomization procedure with random block sizes will be implemented to balance on site and insurance status (public, private, none).

The randomization procedure will be conducted centrally through the DSC. The DSC statistician will generate the randomization schedule using balanced blocks of varying sizes within strata to ensure lack of predictability along with relative equality of assignment across treatment groups. The DSC statistician will review randomization data on a regular basis to ensure that the scheme is being implemented according to plan. A randomization slot, once used, will not be re-allocated.

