#### 12.6.5 Subgroup Analyses

Subgroup analyses will be performed by estimating intervention differences in primary outcomes within subgroups. We are most interested in examining whether the impact of the intervention is modified by treatment seeking (Y/N), insurance (public, private, none), ethnicity/race and rural vs. urban. Two and 3-way interactions of intervention group, time and either treatment seeking, insurance, ethnicity/race or rural/urban status will be added to the weighted GEEs described above. We will estimate ORs and predicted probabilities of treatment engagement comparing XR to SL at each level of the subgroup variable at both 7 and 30 days. Linear contrasts will be used to determine whether the OR comparing XR to SL is modified by the subgroup variable.

In addition, if the results of the ancillary study lead to a mid-study expansion of the eligibility criteria to include those with COWS <8, we will conduct a sensitivity analysis to evaluate its impact. As above, two and 3-way interactions of intervention group, time and an indicator of low vs high COWS (i.e. COWS<8 vs COWS≥8) will be added to the weighted GEEs. Separate ORs comparing XR to SL will be estimated for COWS<8 and COWS≥8 for both 7 and 30 days.

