## 10.2 RCT Component

A sample size of 850 per group/treatment arm was required to ensure 90% power at the two-sided 0.05 significance level to detect a difference in the proportion engaged in formal addiction treatment at Day 7 of 8 percentage points between SL-BUP and XR-BUP, assuming 45% engaged for SL-BUP and 53% engaged for XR-BUP. This is calculated based on a simple two-sample proportion test. This sample size also provides greater than 80% power to detect improvements of 7% (as opposed to 8%). Given the conservative nature of a 45% estimate in the control group (SL-BUP) used, any actual rate in the control group would allow at least 80% power to detect a treatment effect of 7% and at least 90% power to detect a treatment effect of 8%. A sample size of approximately 2,000 was then chosen to accommodate a roughly 15% dropout rate. Power estimates for differing rates in the SL-BUP group and treatment effects are provided in Figure 1.

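### Protocol 12.3 claims sufficient power in named subgroups, but at the plan's own inputs a half-size subgroup has about 65% power for the design effect and smaller subgroups have less

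*Combined protocol and SAP*

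**What the plan says.** Protocol 12.3 sizes the RCT for a single comparison: "A sample size of 850 per group is required to ensure 90% power at the 2-sided 0.05 significance level", for an 8-point difference ("i.e., 45% engaged in SL vs. 53% engaged in XR-BUP"). The total follows from attrition: "We will enroll approximately 2000 patients to accommodate a 15% dropout". The section also claims more than 80% power for a 7-point improvement, whatever the SL-BUP rate. SAP 10.2 names the method: "This is calculated based on a simple two-sample proportion test".

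Protocol 12.3 then extends the claim to subgroups: "This sample size will also provide sufficient power to detect differences in notable subgroups (treatment seeking, rural/urban, insurance Y/N". It does not say how large each subgroup is expected to be, what effect is to be detected, at what power, or by which test. Figure 6 is not reproduced in the text, but its title limits it to 850 per group, which is the whole trial.

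Protocol 12.6.5 plans two kinds of subgroup analysis: XR-BUP vs SL-BUP estimates within each level, and interaction terms in the weighted GEE. Of the latter it says: "Linear contrasts will be used to determine whether the OR comparing XR to SL is modified by the subgroup variable". SAP 10.2 restates the overall power without the subgroup sentence.

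**The concern.** The 850 per arm is close to the number needed for 90% power in the full sample, so little is left over. A subgroup is by definition smaller, and a test that two subgroup effects differ is less precise than either effect alone. A general assurance of sufficient power therefore looks doubtful.

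What is at stake is interpretation. Treatment-seeking status, rural or urban setting and insurance relate closely to the access barriers that motivate XR-BUP in Protocol 3.1 and 4.1. If a subgroup or interaction result is non-significant, a reader who relies on Protocol 12.3 could take it as evidence of no effect, or of no effect modification, when the design had a substantial chance of missing an effect of the planned size.

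**Working it through.** **Inputs from the documents.** 850 evaluable per arm; 45% vs 53%; two-sided 0.05 (Protocol 12.3); 1:1 allocation (Protocol 8.4.4); two-sample test of proportions (SAP 10.2).

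**Inputs assumed.** Subgroup shares, with equal arms inside each subgroup; for the interaction, an 8-point difference between the two subgroup effects. The documents give neither.

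**1. Reproduce the plan's figure.** With n per arm and p̄ = (0.45 + 0.53)/2 = 0.49,

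power = Φ{ [0.08·√n − 1.96·√(2p̄(1 − p̄))] / √(0.45·0.55 + 0.53·0.47) }.

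At n = 850: (2.332 − 1.386)/0.7047 = 1.343, so power is 91.0%. For 7 points it is 82.4%. Attrition: 1700/0.85 = 2000. All three agree with Protocol 12.3.

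**2. Same formula within a subgroup.** At n = 425: (1.649 − 1.386)/0.7047 = 0.374, so power is 64.6%. The last column solves the same formula for the difference from 45% that gives 80% power.

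| Share of patients | n per arm | Power for 45% vs 53% | Difference detectable at 80% power |
|---|---|---|---|
| 50% | 425 | 64.6% | 9.6 points |
| 30% | 255 | 43.9% | 12.4 points |
| 20% | 170 | 31.3% | 15.1 points |
| 10% | 85 | 17.9% | 21.2 points |

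An 8-point effect needs 612 per arm for 80% power, and 612/850 = 72%. A subgroup of about three-quarters of the patients (75%: 637.5 per arm, 82%) therefore passes 80%, but its complement of about one-quarter (212.5 per arm) has 38%.

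**3. Sensitivity of the half-size subgroup.**
- All 2000 evaluable (500 per arm): 72%.
- SL-BUP rate 20%, 30%, 60% or 70% with an 8-point gain: 78%, 69%, 68%, 76%.
- SL-BUP rate 10% or 80%: 92% and 89%.

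The 45% planning rate is close to the least favourable one.

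**4. Effect modification.** Wald test on the difference between two risk differences, with effects of 8 and 0 points and a 45% SL-BUP rate in both subgroups. The variance is the sum of p(1 − p)/n over the four cells.
- 50/50 split: (3·0.2475 + 0.2491)/425 = 0.002333; SE 0.0483; 0.08/0.0483 = 1.656; Φ(1.656 − 1.96) = 38%. On the log-odds scale it is also 38%.
- 20/80 split: (0.2475 + 0.2491)/170 + (2·0.2475)/680 = 0.003649; SE 0.0604; 0.08/0.0604 = 1.324; Φ(1.324 − 1.96) = 26%.
- Interaction detectable with 80% power at 50/50: 13.5 points.
- Other interaction sizes at 50/50: 4 points 13%, 12 points 70%, 16 points 91%.

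These figures include neither any gain from covariate adjustment nor any loss from the weights in the weighted GEE.

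**The case against.** The strongest reply is that the sentence gives no number and so cannot be arithmetically wrong. It does not say 80% or 90%, does not fix the effect at 8 points, and does not say that both levels of each variable are covered. One level of a 75/25 split would have adequate power. This stands in part: the sentence cannot be checked as written, and it would be too strong to call it a miscalculation. But the only standards and the only effect sizes in Protocol 12.3 are 90% for 8 points and 80% for 7 points, and the sentence names whole variables, not favoured levels. On that footing it is unsupported.

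A reader might infer that 65% is the most a half-size subgroup could ever have. The documents do not support that. It is a ceiling for the smaller level over possible splits at the planning rates, but about the floor over SL-BUP rates, and the SAP itself calls 45% conservative.

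A reader might also infer that tests of effect modification have under 40% power in general. That figure depends on the assumed 8-point interaction; one of 16 points would have about 91%. Moreover, the sentence in Protocol 12.3 can be read as referring to effects within subgroups, and Protocol 12.6.5 attaches no power claim to its interaction contrasts.

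Finally, part of the remedy is already planned. SAP 7.2.3 calls for treatment effects with confidence intervals by subgroup. No passage commits the sponsor to reading a null result as no difference, so the harm is a risk of misreading and not a planned error.

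**Conclusion.** The concern holds. Protocol 12.3 states a power property that nothing in the documents supports and that the design lacks at its own planning inputs. For the 8-point effect, the smaller level of any two-way split has at most about 65% power at 45% vs 53% with 850 evaluable per arm, and 18% to 44% at shares of 10% to 30%. Having no dropout, or an SL-BUP rate of 20%, lifts a half-size subgroup to 72% or 78%, still short of 80%; only SL-BUP rates much further from 45% would lift it above. For an assumed 8-point interaction, power is 38% at an even split and 26% at 20/80.

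The sample size re-estimation (Protocol 12.6.4, SAP 11.3) does not repair this. It uses the overall SL-BUP rate and the overall 7- and 8-point effects, and does not consider subgroups.

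It would be wrong to conclude that the trial is underpowered for its primary outcome: that calculation reproduces, and this point does not touch it.

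**What to change.** In Protocol 12.3, delete the subgroup sentence and put in its place:

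> The trial is not powered for subgroup effects or interactions. At a 45% SL rate with 850 evaluable per arm, the difference detectable with 80% power is about 10, 12, 15 and 21 points in subgroups of 50%, 30%, 20% and 10% of participants, and about 14 points for an interaction at a 50/50 split. Subgroup results are reported as estimates with 95% confidence intervals.

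The cost is a protocol wording change and a less favourable stated property. The SAP has no matching sentence to remove, and the design, data collection and analyses stay as they are.
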